#### 1.7.6 Sample Size Estimation

The sample size calculation for this study was calculated based on the primary outcome desire which is willingness for hepatitis C treatment. The sample size calculation will be calculated using the formula for testing the different in proportion between two groups (Lwanga et al., 1991). The formula and calculation are as depicted below:

$$n = \frac{\{[Z_{(1-\alpha/2)} * \sqrt{2\bar{P}(1-\bar{P})}] + [Z_{(1-\beta)} * \sqrt{P_1(1-P_1) + P_2(1-P_2)}]\}^2}{(P_1-P_2)^2}$$

$$n = \frac{\{[1.96 * \sqrt{1.19(1-0.405)}] + [0.842 * \sqrt{0.1875 + 0.2464}]\}^2}{(0.31)^2}$$

$$n = 39$$

Thus, the sample size calculated is equal to 39 for one arm. Total sample size for both control and intervention groups are 78 persons (39 x 2). Following that, an additional adjustment for dropouts were made based on the 77% attrition rate from previous study (Arain et al., 2016). Therefore, the adjustment for response rate is 78/(1-L) (L= attrition rate) = 78/0.33= 236 (118 respondents per arm) (KK Gupta et al., 2016). Thus, the sample size needed for this study is 118 pairs of intervention and control groups which amount to 236 subjects. The information used for sample size calculation is as

presented in Table 3.1. The calculation was based on findings from a randomize control trial study for willingness of hepatitis C treatment (Arain et al., 2016).

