**Table 3.1. Information for sample size calculation**

| Study Characteristic | Assumption made by investigator                                                                                                                        |
|----------------------|--------------------------------------------------------------------------------------------------------------------------------------------------------|
| Type of study        | Randomize Control Trial                                                                                                                                |
| $Z_{(1-\alpha/2)}$   | $Z_{(1-\alpha/2)} = 1.96$ , the value of the standard normal distribution corresponding to a significance level of alpha of 0.05 for a two-sided test. |
| $Z_{(1-\beta)}$      | $Z_{(1-\beta)} = 0.842$ , the value of the standard normal distribution corresponding to the desired level of power of 80%.                            |
| $P_1$                | $P_1 = 0.75$ , Proportion of respondent willing for treatment in intervention group at 3 months post intervention                                      |
| $P_2$                | $P_2 = 0.44$ , Proportion of respondent willing for treatment in control group at 3 months post intervention                                           |
| $\bar{P}$            | $\bar{P} = (0.75 + 0.44) / 2$ , $\bar{P} = 0.595$                                                                                                      |

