### **1.15 Data Analysis**

#### **1.15.1 Statistical Test in Data Analysis**

Data collected will be analysed using IBM SPSS (Version 27.0). Data exploration will be performed to look for any error in data entry, missing data and presence of outliers.

The distribution of numerical data will then be determined whether they are normally or not-normally distributed. In determining the normality of data both statistical and graphical method will be use. For statistical method, the Skewness/SE of skewness and the Kolmogorov-Smirnov parameter will be calculated, while for the graphical method, the histogram together with stem and leaf box plot will be plotted and analyses. Furthermore, after determining the normality of data, mean and standard deviation will use to described normally distributed data, while median with first and third quartile (Q1, Q3) will be used to described not normally distributed data. Categorical data will be presented as frequency and percentage.

For between group comparison, the independent sample t-test will be used to compare the mean different of continuous and normally distributed data between intervention and control group. For continuous but not normally distributed data, the Mann-Whitney U test will be used to compare between intervention and control group. The Chi-square test will be used to compare frequency different of categorical data between intervention and control groups and for data of 2 by 2 table that contains cell with an expected count less than 5 for more than 20%, the Fisher's exact test will be use.

For within group changes overtime comparison, the One-way repeated measure ANOVA will be used for continuous and normally distributed variables. Within group analysis for categorical data will use the Cochran's Q test.

The Generalized Linear Mixed Model (GLMM) will be used to test the main effect and interaction between and within the intervention and control groups overtime (baseline, immediately post intervention, and 3-month post intervention). This study will use a significance level with a *p*-value of 0.05 and a confidence interval of 95% for hypothesis testing. For results yielded *p*-value of less than 0.05 will be consider as statistically significant findings.

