#### **1.15.2 Strategy of Data Analysis**

This study will adopt the intention to treat analysis strategy during data analysis. Intention to treat analysis is a method for analysing results in a randomized study where all participants who are randomized are included in the statistical analysis and analysed according to the group they were originally assigned, regardless of what treatment they received.

In handling missing data, the type of missing data will be first identified whether it is missing completely at random (MCAR), missing at random (MAR) or missing not at random (MNAR). Several techniques exist in handling missing data such as listwise or case deletion, pairwise deletion, mean substitution, regression imputation, last observe case carried forward, maximum likelihood, expectation-maximization (EM) and multiple imputation.

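### The within-arm tests named in 1.15.1 use only clients seen at all three visits unless missing visits are imputed, which does not fit the all-randomised rule in 1.15.2

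*Protocol*

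**What the plan says.** Objectives iii.i and iv.i (Protocol 1.2.2) ask for change within each arm from baseline to immediately after the intervention (T1) and to three months (T2), for willingness and for the four scores. Hypotheses H1 to H5 (1.3) each include a within-group claim.

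Section 1.15.1 names the tests for this. For scores, "the One-way repeated measure ANOVA will be used for continuous and normally distributed variables". For yes/no data, and so for willingness, the primary outcome, "Within group analysis for categorical data will use the Cochran's Q test". The same section adds a generalised linear mixed model (GLMM) that "will be used to test the main effect and interaction between and within the intervention and control groups overtime".

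Section 1.15.2 adopts intention to treat, under which "all participants who are randomized are included in the statistical analysis and analysed according to the group they were originally assigned". It then lists ways of handling missing data, from listwise deletion through last observation carried forward to multiple imputation, and chooses none.

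Section 1.7.6 plans for heavy loss: "an additional adjustment for dropouts were made based on the 77% attrition rate from previous study".

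**The concern.** Cochran's Q and the classical repeated-measures ANOVA work on complete rows. On the data as collected, a client with baseline and T1 but no T2 is removed entirely, including from the baseline-to-T1 question for which both answers exist. By 1.13, T1 in the control arm falls only one to two weeks after baseline, and in the intervention arm it follows a session held within one to two weeks, so many later dropouts could have both. The GLMM in the same section keeps those visits. One objective is therefore answered twice, on two populations, with no order of precedence, and only one of the two answers meets the population rule in 1.15.2.

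At stake is a within-arm result that is labelled intention-to-treat but describes the minority who stayed. If staying is related to the T1 answer, that result can show change where there is none.

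**Working it through.** **Inputs from the documents.** Alpha is 0.05 two-sided and power 80%; willingness at three months is 0.75 (intervention) and 0.44 (control) (Table 3.1). The plan has 39 per arm before dropout, stated attrition of 77%, a divisor of 0.33, and 118 per arm after inflation (1.7.6).

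**The plan's own figures.** With mean proportion 0.595, n = [1.96 × √(1.19 × 0.405) + 0.842 × √(0.1875 + 0.2464)]² / 0.31² = 38.2, which rounds up to the stated 39. For dropout, 78 / 0.33 = 236.4 gives the stated 236, or 118 per arm. Attrition of 77% would instead mean 78 / 0.23 = 339.1, so 340. The 118 therefore rests on 67% attrition, not 77%.

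**Complete clients per arm**
- At the stated 77%: 118 × 0.23 = 27.1, about 27.
- At the 67% implied by the divisor: 118 × 0.33 = 38.9, about 39.

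Both assume that the trial loses clients at the planning rate.

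**Power of Cochran's Q on complete clients.** These are simulations of three correlated yes/no visits from a latent normal model. The latent correlation of 0.5 is an assumption; the documents give none. Willingness moves from baseline to a common value at T1 and T2.

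| Change | n = 27 | n = 39 | n = 118 |
|---|---|---|---|
| 0.44 to 0.60 | 29% | 41% | 88% |
| 0.44 to 0.65 | 47% | 65% | 99% |
| 0.44 to 0.75 | 85% | 95% | about 100% |

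For 0.44 to 0.75, varying the correlation over 0.3, 0.5 and 0.7 gives 78%, 85% and 92% at n = 27, and 91%, 95% and 99% at n = 39. The n = 118 column assumes that no visit is missing. It is only an upper bound for the GLMM, which gains the observed T1 answers of later dropouts but no missing T2 values.

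**Bias when dropout depends on the T1 answer.** Take an arm with no true change, willingness 0.44 at every visit. Assume that 60% of clients answering yes at T1 and 90% of those answering no are lost before T2.
- Fraction retained: 0.44 × 0.40 + 0.56 × 0.10 = 0.176 + 0.056 = 0.232, or about 27 of 118.
- T1 willingness among those retained: 0.176 / 0.232 = 0.76.
- Baseline and T2 willingness among those retained (simulated, correlation 0.5): 0.55 and 0.55.

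Completers thus show 0.55, 0.76, 0.55 where the truth is flat. Cochran's Q at nominal 5% rejects in about 49% of simulated trials. With weaker dependence (70% of yes, 83% of no) it rejects in about 12%; with dropout unrelated to the answer, in 5%. In this model the distortion falls on the T1 comparison, and baseline-to-T2 change is hardly moved.

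Under the 60%/90% rates, with true willingness 0.44, 0.75, 0.75, completers in the intervention arm have T1 willingness (0.75 × 0.40) / (0.75 × 0.40 + 0.25 × 0.10) = 0.300 / 0.325 = 0.92 and simulated baseline willingness 0.50. The apparent T1 gain is about 0.42 against a true 0.31.

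**The case against.** The strongest reply is that the protocol nowhere restricts these tests to completers. Section 1.15.2 lists imputation methods, and with a filled data set all 118 per arm could enter both tests. Which method is chosen is commonly left to an analysis plan, which is not at hand. This stands as far as it goes: completers-only is a property of the tests on unimputed data, and a reader who inferred that the protocol prescribes it would be wrong. But nothing in the protocol requires imputation, and listwise deletion is on the same list. The protocol itself fixes both the tests and the population, and they agree only under a choice it does not make.

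A second reply is that quoting 27 of 118 alone pairs 23% retention with a sample size built on 33%. That is correct, and the range of 27 to 39 should be given.

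Third, a reader might take the drop from 88% power at n = 118 to 29% at n = 27 as the price of these tests. The documents do not support that. The smaller effect is not the planned one, the GLMM cannot recover unobserved T2 answers, and at the planned effect power stays near or above 80% over the range examined.

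Fourth, the GLMM already covers within-group change, and within-arm tests are not the randomised comparison. Both statements are true, and they limit the severity. They do not settle which of the two within-arm answers counts.

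**Conclusion.** The point holds in a limited form. Unless missing visits are imputed, the tests named for objectives iii.i and iv.i would use about 27 to 39 of 118 clients per arm if the planning attrition occurs, contrary to the all-randomised rule. Loss of power is secondary: it matters for effects smaller than planned (29% to 41% for 0.44 to 0.60) and not much for 0.44 to 0.75. The main risk is a false within-arm finding at T1, with rejection rates from 5% to about 49% depending on how strongly dropout follows the T1 answer. Those dropout rates and the latent correlation are assumptions; the protocol gives no information on either. The same mechanism would apply to the scores under repeated-measures ANOVA, but its size was not calculated.

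It might be inferred that the trial's conclusion on effectiveness is undermined. The documents do not support that: between-group tests and the GLMM interaction carry that conclusion. Severity is minor to moderate.

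**What to change.** In 1.15.1, make the within-arm contrasts from the planned GLMM (T1 minus baseline and T2 minus baseline, as estimates with 95% CIs) the analysis for objectives iii.i and iv.i. Fit the model to all observed visits of all randomised clients, with a logit link for willingness and the corresponding model for each score. If Cochran's Q and repeated-measures ANOVA are kept, call them completers-only supplementary results, report their n, and do not describe them as intention-to-treat. When the expected number of completers is quoted, state which attrition figure it uses, because 77% and the 0.33 divisor in 1.7.6 disagree.

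The cost is one paragraph of wording, with no extra data or clients, since the model is already planned. The small downside is that the contrasts rest on a missing-at-random assumption and a correctly specified model. They remain exposed if dropout depends on answers that were never observed.

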#### **1.15.2 Strategy of Data Analysis**

This study will adopt the intention to treat analysis strategy during data analysis. Intention to treat analysis is a method for analysing results in a randomized study where all participants who are randomized are included in the statistical analysis and analysed according to the group they were originally assigned, regardless of what treatment they received.

In handling missing data, the type of missing data will be first identified whether it is missing completely at random (MCAR), missing at random (MAR) or missing not at random (MNAR). Several techniques exist in handling missing data such as listwise or case deletion, pairwise deletion, mean substitution, regression imputation, last observe case carried forward, maximum likelihood, expectation-maximization (EM) and multiple imputation.

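### Missing-data handling starts from classifying the mechanism as MCAR, MAR or MNAR, which observed data cannot complete; with the planned attrition, the technique then left open can decide the 3-month result

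*Protocol*

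**What the plan says.** Section 1.15.2 of the protocol makes three statements that bear on this point.

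- The analysis follows intention to treat: "all participants who are randomized are included in the statistical analysis".
- Before missing data are handled, "the type of missing data will be first identified whether it is missing completely at random (MCAR), missing at random (MAR"; MNAR is the third class named. This is written as something that will be done.
- "Several techniques exist in handling missing data such as listwise or case deletion, pairwise deletion, mean substitution, regression imputation, last observe case carried forward", followed by maximum likelihood, EM and multiple imputation. No technique is chosen or ruled out, and nothing links a mechanism to a technique.

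Section 1.15.1 states that "The Generalized Linear Mixed Model (GLMM) will be used to test the main effect and interaction" between and within groups over baseline, immediate post-intervention and 3 months. It does not say that this model is also the answer to missing data. The same section plans chi-square or Fisher tests between groups and Cochran's Q within groups for categorical outcomes.

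Section 1.7.6 sets the amount of missing data to expect: "an additional adjustment for dropouts were made based on the 77% attrition rate from previous study". The arithmetic there is "78/0.33= 236 (118 respondents per arm", so the divisor used corresponds to 67%. Table 3.1 places the planning proportions, 0.75 and 0.44, at 3 months.

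**The concern.** MAR and MNAR differ in whether missingness still depends on the unseen values once the seen ones are taken into account. No test on the collected data can settle that. Data can speak against MCAR, for example if dropouts differ from completers in their baseline answers, but the three-way classification that the section requires cannot be finished. A statistical analysis plan that followed the protocol faithfully would inherit an instruction that nobody can carry out.

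The classification, such as it is, can only be attempted once outcome data are in. The choice of technique that would follow it is therefore open at a point when the consequences of each option are visible.

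In a trial with few losses this would be a small matter. Here two thirds or more of the 3-month willingness answers are expected to be missing, and that is the time point on which the sample size rests.

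**Working it through.** **Inputs.** From section 1.7.6 and Table 3.1: P1 = 0.75, P2 = 0.44, two-sided alpha 0.05, power 80%, 118 per arm, attrition 77% stated and 1 − 0.33 = 67% implied. The documents give no willingness rates at baseline or T1 and no timing of dropout, so those are assumptions below.

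**The plan's own figures.** With mean proportion 0.595, n = {1.96 × √(1.19 × 0.405) + 0.842 × √(0.1875 + 0.2464)}² / 0.31² = 38.2, so "Thus, the sample size calculated is equal to 39 for one arm" reproduces. The inflation does not: 78/0.23 = 339.1, that is 340, whereas 236 needs the divisor 0.33. That mismatch is a separate matter; both rates are carried through here.

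**Observed at 3 months.**
- 77%: 118 × 0.23 = 27 per arm, 91 missing.
- 67%: 118 × 0.33 = 39 per arm, 79 missing.

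**One dataset, several techniques from the list.** Suppose the 27 completers per arm show exactly 0.75 and 0.44 (two-proportion z-test on expected counts).

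| Technique | Difference | p |
|---|---|---|
| Complete cases | 0.31 | 0.020 |
| Overall-mean substitution | 0.31 × 27/118 = 0.07 | 0.27 |
| Arm-mean substitution | 0.31 | about 0.000001 |
| Baseline carried forward (equal in both arms, 0.30 to 0.60 assumed) | 0.07 | 0.26 to 0.28 |
| T1 carried forward (control 0.44, intervention 0.75 to 0.95 assumed) | 0.31 to 0.46 | < 0.00001 |

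If the 91 missing answers per arm may take any value, the difference lies between (20.25 − 11.88 − 91)/118 = −0.70 and (20.25 + 91 − 11.88)/118 = +0.84.

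**Last observation carried forward when the effect has faded.** Assume a gap of 0.31 at T1, none at T2, and 0.44 in both arms at baseline. Spurious T2 gap = missing fraction × share of dropouts lost after T1 × 0.31.

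| Share lost after T1 | 77% missing | 67% missing |
|---|---|---|
| All | 0.77 × 0.31 = 0.24 | 0.67 × 0.31 = 0.21 |
| Half | 0.12 | 0.10 |
| None | 0 | 0 |

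In simulation at 77% missing, the z-test rejects in about 97%, 44% and 5% of trials respectively. At 67% missing with all lost after T1, it rejects in about 90%.

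**Mean substitution when there is no effect** (0.44 in both arms, nominal 5%).
- Arm means, variance taken from the filled-in values: the standard error shrinks by roughly the retained fraction, so type I error ≈ 2P(Z > 1.96 × 0.23) = 0.65; simulated about 68%. At 67% missing, 2P(Z > 1.96 × 0.33) = 0.52; simulated 52% to 57%.
- Arm means, chi-square-type variance p(1 − p)/118: 2P(Z > 1.96 × √0.23) = 0.35; simulated about 34%. At 67% missing, 2P(Z > 1.96 × √0.33) = 0.26; simulated about 31%.
- Overall mean: no inflation (about 5% with a t-test). The estimate is pulled toward zero instead, as in the first table.

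**The case against.** The strongest reply is that section 1.15.2 commits to very little. It says that techniques exist; it does not say they will be used, and the list includes maximum likelihood, EM and multiple imputation. Leaving the choice to a statistical analysis plan is normal practice. All of this stands, and it limits the point in three ways.

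- A reader might infer that the trial plans to carry answers forward or to substitute means. The text does not support that; these methods are named and not adopted.
- A reader might infer that listing "listwise or case deletion, pairwise deletion, mean substitution, regression imputation, last observe case carried forward" contradicts the intention-to-treat sentence in the same section. It would if deletion were chosen, but it is only mentioned, so no contradiction is shown.
- A reader might infer that the mechanism cannot be examined at all, or that a false positive is nearly certain. Evidence against MCAR can be obtained. The largest error rates need particular assumptions: every dropout completing T1 and a full T1 gap that vanishes by T2, or arm-specific means with the variance taken from filled-in values. Section 1.13 puts one to two weeks between baseline and the session, so some losses could precede T1, and then the carried-forward bias shrinks or disappears.

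The reply does not cover the classification step itself. That is a stated commitment that cannot be met, not a detail left for later.

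**Conclusion.** The point holds as a badly fixed rule. The protocol makes handling begin with a classification that observed data cannot complete, follows it with an open list that mixes sound and unsound techniques, and does not connect the GLMM it already plans to the missing-data problem.

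The stake is large under either attrition figure. On one and the same set of completers at the planning rates, listed techniques give p-values from about 0.000001 to about 0.27. The direction of any error is not known in advance: carrying T1 forward or using arm means can create or exaggerate an effect, while carrying baseline forward or using the overall mean can hide one. The simulated and analytic sizes rest on the assumed baseline and T1 rates, dropout timing and test, and show what could happen, not what will. If real attrition were far below the planning figure, the effect of the choice would be much smaller.

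**What to change.** In section 1.15.2:

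1. Delete identification of the mechanism as the basis for handling missing data. Comparing dropouts with completers can stay as description.
2. State that the 3-month willingness comparison comes from the GLMM already planned in 1.15.1, with a logit link, using all available T0, T1 and T2 answers of every randomised participant, under a stated MAR assumption.
3. Remove mean substitution, single regression imputation and last observation carried forward as options for the primary outcome.
4. Add one prespecified MNAR sensitivity analysis: delta-adjusted multiple imputation over a stated range of shifts that may differ by arm, reported as a tipping point. Treating missing as not willing in both arms can be one scenario. It is not the extreme case, because the bounds of −0.70 and +0.84 arise from opposite assumptions in the two arms.

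The cost is revised wording, one extra analysis and possibly a wider confidence interval. No new participants or data are needed.
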